### Family history and supplementary information

The average height of the participants was 142.51 ± 11.01 cm, and the mean value of weight was 35.21 ± 9.09 kg. According to the feedback from guardians, 72% of fathers and 76% of mothers had myopia. Among the 100 families, both parents had myopia, accounting for 58%, and only 10% had nonmyopic parents.Most parents graduated from university and above (81% for fathers and 83% for mothers). Only 7% of fathers and mothers have a secondary school degree or less. Of the 100 participants, 73 reported that their first correction of myopia was 8.41 ± 1.54 years, and the remaining 27 participants reported that they had never found or corrected myopia before. Forty—six participants had provided personal information about hobbies. Based on the responses from participants, hobbies were divided into three categories: outdoor activities, indoor activities and near work activities. The percentages for each category were 15%, 22% and 63% respectively. The most commonly reported activities were near work activities, including playing piano/guitar/lego/guzheng/chess, reading, drawing and watching television. This was followed by indoor activities, including swimming, dancing, singing, skating, taekwondo and playing ping pong. The outdoor activities included playing dadminton/soccer, skiing and bicycle riding.

## Discussion

Although numerous interventions are currently available to slow myopia progression, it still be beneficialfor young children to develop effective and safe strategies for myopic retardation. Spectacle lenses with contiguous aspherical lenslets may be an interesting option. At present, there are few reports on the myopia control effect of these lenses. From this perspective, we conducted a double-masked, crossover, randomized clinical trial to assess the efficacy of spectacle lenses with rings of contiguous slightly aspherical lenslets.

We followed 100 children randomized into two groups of 50. The two groups were well matched for the main covariate parameters, such as age, spherical equivalent refractive error, and AL (0.49 < p < 0.94), minimizing their effects on the results of the study.

In this study, we adopted a one-year crossoverdesign that is not very common in myopia research. We believe that this approach has merit, particularly for completely novel interventions whose myopia control effect is difficult to infer from previous studies. Unlike regular clinical trial design, this crossoverdesign may provide a within-subject treatment comparison with little to no influence of genetics and other subject-specific factors. However, it must be noted that these analyses should be interpreted with caution because they may be biased by possible carry-over effects or difficulty with subject masking.

We also opted to have a shorter interval (maximum of 3 months) between the study visits; that is, a maximum of 3 months versus the more standard 6 months. This decision was motivated by the interest in evaluating the myopia control effect of SAL lenses at finer temporal resolution. Although cycloplegic SER and AL are only taken at baseline, and at the 6- and 12-month visits to minimize cycloplegia, we believe that these data will provide valid evidence for the effect of myopia control.Moreover, AL without cycloplegia will be taken at the 3-, 5-, and 9-month visits, and these data will be informative. First, the AL is considered animportant index to evaluate myopic progression [34, 35]. Second, previous research has indicated that (lack of) cycloplegia has no significant effect on AL [36]. In addition, 3-month visits may allow better compliance through parent and child engagement and, more often, equipment checks.

In general, the children adapted well to both SAL and single vision lenses. According to the results of the questionnaire, there were some small but statistically significant differences in the clarity of vision and vision satisfaction between the two spectacle lens types. Although children rated the clarity of vision and overall visual satisfaction higher with SVL, the SAL lenses did not aggravate the severity of blur or induce higher discomfort. Moreover, the mean values were above 9 in both groups and the differences were 0.23 for clarity of vision and 0.19 for vision satisfaction. Considering that the values came from a questionnaire with a 1 to 10 score, these differences are likely clinically irrelevant.

According to spontaneous verbal feedback of SAL group wearers, five of the children reported slight perception of blur in the peripheral vision, and two children reported blur when reading, but they adopted a strategy to obtain a clear image. One child felt dizzy on the first day of using the SAL lens. In all these children, the adaptation did not exceed one day, and none of them discontinued the trial because of an adaptation problem.

To ensure the accuracy of the DCVA, measurements were taken using an ETDRS logMAR chart at 4 m under stable room lighting conditions. Although the corrected visual acuity was slightly better with single vision lenses, we did not find a significant difference between SAL lenses and single vision lenses. The SAL lenses do not compromise DCVA.

Previous studies have confirmed the relationship between time spent outdoors and the prevalence of myopia. Outdoor activity is a protective factor against the development of myopia [37]. Of 46 participants, only 7 reported that their hobbies were outdoor activities. Unfortunately, the data on the time and frequency of outdoor activities were not collected in this study. Another risk factor is parental history of myopia. Children with myopic parents had a higher risk of developing myopia [38]. The prevalence of parental myopia was high in this study. 58% of participants had two myopic parents, and 32% of participants had one myopic parent, which were much higher than that in Ip JM et al.’s survey. The possible reasons were the differences in the race, region and inclusion criteria of participates.

Another detail that should be noted was that we did not dispense new equipment, even though the degree of myopia may have progressed at 3 months and 9 months (V3 and V6). One thing that needs to be considered is whether undercorrection will accelerate myopic progression. Previous studies demonstrated that undercorrection produced no significant difference in myopia progression compared with full correction [39, 40]. Chung K et al. reported that undercorrection produced myopia progression [41]. However, the difference between undercorrection and full correction was slight (-0.23 D) over the 24-month research period. We speculated that undercorrection in the short-term would not accelerate the progression of myopia.

One limitation of this study was failure to collect the environmental factors, such as time and frequency of outdoor activities. Environmental factors played an important role in myopia based on several epidemiological studies. But all participants were randomly recruited and assigned to two groups, which could reduce the impact of bias. Another limitation was the lack of information on the prior year’s myopia progression. However, the main purpose of this study was to evaluate the control effect of SAL lenses, rather than to analyze related factors. Further studies should be designed to observe the influence of environmental and prior progression factors on myopia control effect of such spectacle lenses.

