**Conclusions:**

The children in the two well balanced groups had comparable visual acuity and adapted well to the test lenses. These results imply that visual acuity can be well improved by SAL lenses. Clear visual acuity provides the assurance for good compliance in this longitudinal study.

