### Study participants

A total of 100 children were recruited from the hospital into this study between January and March 2019. The inclusion criteria were best-corrected visual acuity equal to or better than 1.0, age between 8 and 13 years inclusive, spherical equivalent of cycloplegic autorefraction between -0.75 D to -4.75 D in each eye, astigmatism no more than 1.50 D, anisometropia no more than 1.00 D, and absence of strabismus. Subjects with a history of ocular or systemic disease, history of wearing PALs, or prior myopia control treatment were excluded from participation in the study.

The study was designed to achieve 80% power to detect a minimum difference of 0.27 D with an SD of 0.37 D at 6 months at a 5% level of significance. Using an online sample size calculator by the Clinical & Translational Science Institute33, the theoretical sample size was 42 with a 1:1 sample ratio in each group. Allowing a maximum drop-out rate of 15%, the number to be recruited for each group was estimated to be 50.

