### Lens adaptation

All subjects adapted well to both SAL lenses and single vision lenses (Table 4). The mean DCVA at the dispensing visit was 0.06 ± 0.08 logMAR (range: -0.14 to 0.24 logMAR) in Group 1 (SAL lenses) and 0.04 ± 0.05 logMAR (range: -0.1 to 0.14 logMAR) in Group 2 (single vision lenses, SVL), with no significant difference between the groups (t = 1.11, *p* = 0.27).

**Table 4 Tab4:** Adaptation to the SAL and single vision lenses. *DCVA* Distance-corrected visual acuity. Data expressed as the mean ± SD. Group 1: in phase one for Group 1, the subjects wear the SAL lenses; Group 2: in phase one for Group 2, the subjects wear single vision lenses (SVL)

	SAL	SVL	t value	*p* value
DCVA	0.06 ± 0.08	0.04 ± 0.06	1.11	0.27
Perception of ghost images	1.04 ± 0.20	1.00 ± 0.00	1.43	0.16
Comfort of spectacles	9.68 ± 0.55	9.84 ± 0.42	-1.64	0.11
Clarity of vision	9.70 ± 0.58	9.93 ± 0.25	-2.59	0.01
Vision satisfaction	9.72 ± 0.50	9.91 ± 0.29	-2.32	0.02

For the perception of ghost images, we found no significant difference between the lens types (mean values: 1.04 ± 0.20 for SAL lenses and 1.00 ± 0.00 for SVL lenses; t = 1.43, *p* = 0.16). Similarly, there was no significant difference in the comfort of the spectacles (mean values: 9.68 ± 0.55 for SAL lenses and 9.84 ± 0.42 for SVL lenses; t = -1.64, *p* = 0.11). Regarding clarity of vision and vision satisfaction, small but significant differences were observed between the two lens types. The subjects rated single vision lenses as providing higher clarity of vision (mean values: 9.70 ± 0.58 for SAL lenses and 9.93 ± 0.25 for SVL lenses; t = -2.59, *p* = 0.01) and vision satisfaction (mean values: 9.72 ± 0.50 for SAL lenses and 9.91 ± 0.29 for SVL lenses: 0.19; t = -2.32, *p* = 0.02).

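### A non-significant acuity test at dispensing (p = 0.27) is read as no acuity loss, and as improvement, with SAL lenses; neither conclusion follows from it

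*Protocol article*

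**What the plan says.** Distance-corrected visual acuity (DCVA) is listed under Secondary outcome measures. It is scored at 0.02 logMAR per letter, and Table 1 schedules it at every visit.

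The Lens adaptation section of the Results gives the dispensing-visit data: "The mean DCVA at the dispensing visit was 0.06 ± 0.08 logMAR (range: -0.14 to 0.24 logMAR) in Group 1 (SAL lenses"), against "0.04 ± 0.05 logMAR (range: -0.1 to 0.14 logMAR) in Group 2" (SVL), "with no significant difference between the groups (t = 1.11, *p* = 0.27"). Table 4 repeats the comparison but prints the SVL standard deviation as 0.06.

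The Discussion first says "Although the corrected visual acuity was slightly better with single vision lenses, we did not find a significant difference" between the lenses. It then concludes, without qualification, "The SAL lenses do not compromise DCVA".

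The Abstract's Conclusions call acuity in the two groups comparable and state "These results imply that visual acuity can be well improved by SAL lenses". They go on to treat clear acuity as an assurance of good compliance in the trial.

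**The concern.** There are two separate faults of inference.

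1. **No difference detected becomes no loss.** The t test asks whether the means differ. A p value of 0.27 says only that a difference was not shown. A claim of no loss needs an interval read against a stated margin, and the article gives neither. The trial was also sized on refraction (0.27 D, SD 0.37 D), not on acuity.

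2. **Improvement is claimed without a before/after comparison.** Presenting acuity and DCVA were taken at the baseline visit, but the article prints no uncorrected, presenting or pre-lens acuity value. A comparison between two lenses worn by different children cannot show that either one improved acuity.

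These are conclusions that the article itself states, one of them in the abstract. They are not details left to a fuller document. A reader could take it as settled that the lens has no acuity cost.

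**Working it through.** **Inputs.** From Lens adaptation and Table 4: SAL 0.06 ± 0.08; SVL 0.04 ± 0.05 (text) or ± 0.06 (table); t = 1.11, p = 0.27. From Between-group comparison of baseline data: two groups of 50. Neither the text nor Table 4 gives an n for DCVA, so 50 per group is an assumption, tested in step 5. The difference is SAL minus SVL, so a positive value means worse acuity with SAL.

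**1. Reproduce the reported test.** On 98 df, t = 1.11 gives p = 0.270, as printed.
- SE = √[(0.08² + 0.05²)/50] = 0.01334, or √[(0.08² + 0.06²)/50] = 0.01414.
- The rounded means give t = 0.02/0.01334 = 1.50 (p = 0.14) or 0.02/0.01414 = 1.41 (p = 0.16), not 1.11.
- Two-decimal rounding allows a true difference between 0.01 and 0.03. A difference of 1.11 × SE = 0.0148 or 0.0157 lies inside that range, so the reported t is consistent with the printed means.

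**2. Recover the interval.** 95% CI = difference ± 1.984 × SE.

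| Basis | SVL SD | Difference | 95% CI (logMAR) |
|---|---|---|---|
| t = 1.11 | 0.05 | 0.015 | -0.012 to 0.041 |
| t = 1.11 | 0.06 | 0.016 | -0.012 to 0.044 |
| printed means | 0.05 | 0.020 | -0.006 to 0.046 |
| printed means | 0.06 | 0.020 | -0.008 to 0.048 |

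The upper limits divided by 0.02 are 2.05 to 2.4 letters.

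**3. Effect of rounded SDs.** Given t = 1.11, the upper limit is (1.11 + 1.984) × SE. At the largest SDs that round to the Table 4 values (0.085 and 0.065), SE = √[(0.085² + 0.065²)/50] = 0.01513 and the limit is 0.047. It stays below 0.05.

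**4. What the test could detect.** Power ≈ Φ(δ/SE - 1.96). For a one-letter mean loss (δ = 0.02) this is Φ(-0.46) = 32% or Φ(-0.55) = 29%. For 0.04 logMAR it is 81 to 85%, and for 0.05 it is 94 to 96%. The article sets no margin. Read against assumed margins, the intervals do not show non-inferiority at 0.02 or 0.04 logMAR, just show it at 0.05, and clearly show it at 0.10.

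**5. Effect of n.** Table 4 gives SVL questionnaire means of 9.93 and 9.91. If ratings are whole numbers, 50 children would total 496.5 and 495.5, which is impossible, so fewer than 50 SVL children may have answered the questionnaire. If DCVA had, for illustration, 44 SVL children, the pooled-variance upper limits would be 0.043 to 0.049. The reading does not change.

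**6. Improvement.** No arithmetic applies, because no reported figure compares acuity before and after a lens.

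**The case against.** The strongest reply is that nothing in the trial depends on these sentences. DCVA is secondary, and the planned comparisons under Prospective data analyses concern refraction and axial length. Compliance is asked directly in questions 5 and 6 of the study equipment questionnaire, so no analysis rests on the acuity inference. The article also discloses the direction: it says acuity was slightly better with SVL, reports lower clarity and satisfaction ratings with SAL, and prints the means, SDs, ranges, t and p from which the interval can be recovered. That interval is fairly reassuring. All of this stands, and it sets the severity. It does not rescue a flat statement of no compromise, and it leaves the improvement sentence without any figure behind it.

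A reader might be tempted by three stronger readings, none of which the document supports:

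- **That some children lose acuity with SAL, because the spread is wider.** The SAL range, -0.14 to 0.24, extends further than the SVL range, -0.1 to 0.14, at both ends, including the better end. The groups are different children and no baseline DCVA by group is printed, so the spread cannot be attributed to the lens. A variance-ratio test, or percentages beyond a cut-off under normality, would rest on SDs rounded to one significant figure. At the rounding limits of the Table 4 SDs (0.075 against 0.065) the variance ratio is 1.33, p = 0.32.
- **That means of 0.06 and 0.04 contradict the entry criterion**, "best-corrected visual acuity equal to or better than 1.0". That criterion concerns best-corrected acuity at screening. DCVA was measured on an ETDRS chart at dispensing, about a month later. The gap is seen with both lenses, so it says nothing about SAL.
- **That SAL harms acuity.** The interval includes zero.

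**Conclusion.** The point holds as a fault of inference and wording. The data support a statement that no difference in mean high-contrast DCVA was detected at dispensing and that a mean loss above about 0.05 logMAR (2.5 letters) is unlikely. They do not support a flat claim of no loss, because a mean loss of about 2 letters lies within the interval, and they contain nothing on improvement.

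The size rests on about 50 children per group and on summary figures printed to two decimals. Neither the choice of SVL SD, nor rounding of the SDs given the reported t, nor a moderately smaller SVL group moves the upper limit past 0.05. Severity is minor.

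**What to change.** - In the Discussion, replace the no-compromise sentence with the SAL minus SVL difference, its 95% CI and the n analysed in each group. Limit the conclusion to: no difference in mean high-contrast DCVA detected at dispensing; mean loss above about 0.05 logMAR unlikely. The exact bound should come from the unrounded data.
- In the Abstract's Conclusions, delete the improvement sentence.
- Reconcile the SVL standard deviation between the Lens adaptation text (0.05) and Table 4 (0.06).
- For any later claim of no acuity loss, use the within-child SAL minus SVL contrast after crossover, against a margin fixed before that analysis. DCVA is scheduled at every visit and each child wears both lenses, so no new measurement is needed. A margin can no longer be set in advance for the dispensing data, which are already reported; for those, give the interval only.

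The cost is a few sentences and one small calculation on data already collected. The downside is a more modest acuity claim.

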## Conclusion

In conclusion, lenses with contiguous aspherical lenslets are an emerging opportunity for myopia control. With the exception of the adaptation problem in the initial stage of using SAL lenses, this type of lens could be well adapted. If SAL lenses are capable of slowing myopia progression, they will provide a safe and effective optical strategy option for children.

## Data Availability

The data that support the findings of this study are not publicly available because they contain information that could compromise the privacy of research participants, but are available from the corresponding author ([name]) upon reasonable request.

## Abbreviations

SAL: Slightly aspherical contiguous lenslets technology
Ortho-K: Orthokeratology
PALs: Progressive addition spectacle lenses
AL: Axial length
SER: Spherical equivalent of autorefraction
CT: Corneal thickness
ACD: Anterior chamber depth
LT: Lens thickness
DCVA: Distance-corrected visual acuity
ETDRS: Early treatment diabetic retinopathy study
NPC: Near and far phoria, near point of convergence
SVL: Single vision lenses
